## Trial design

A multicenter, prospective, parallel-group, cluster-randomized controlled, superiority trial will be conducted (see Figs. 1 and 2). The study will be carried out over 12 months (1 year) of intervention (i.e., the continuing education program) delivery and follow-up. Drugstores and drugstores/pharmacies (the clusters) will be randomized at a 1:1 ratio to enroll in either the intervention group or the control group. The geography zone (neighborhoods) will be randomized stratified.

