### Sample size

A study carried out in Spain evaluated the competences pharmacists, principally the knowledge before and after an educational intervention facilitated by pharmacists, finding that the intervention increases in 37% the knowledge of the pharmacists who attended the course [23]. Therefore, the continuing education program is expected to improve the pharmacy staff competencies in the intervention group at least 30% and in the control group by 15% (less in improving or increasing competencies). With a confidence level of 95% and a power of 80% and superiority design, it was calculated that it is necessary to include at least 121 drugstores or drugstores/pharmacies in each group. To cover losses to follow-up, the sample was increased by 10%, increasing the sensitivity for the fulfillment of secondary objectives; the size of the final sample will be 135 drugstores or drugstores/pharmacies for each group (1:1 ratio).

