### Data collection

Data will be collected between December 2018 and December 2019, conducted over 12 months of intervention delivery and follow-up. The data obtained in this study will be registered in an electronic database. The effectiveness of the continuing education program will be assessed before and after the intervention. The same questionnaires will be used in T0 and T12 for the pharmacy staff and the patients or caregivers. An additional measurement will be made for the intervention group 12 months after the end of the follow-up time in order to evaluate the effects of the educational intervention over time. All measuring instruments will be reviewed and adjusted by a group of 10 experts. Three different sessions will be carried out, in which the questionnaire will be presented, and the experts will be asked for their opinions regarding the relevance of the content of the items (content validity).

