### Statistical methods

Baseline and demographic characteristics will be analyzed descriptively. All primary and secondary outcomes will be compared in pre-post analyses and between-group comparisons. Comparisons for categorical variables will be conducted by using the chi-square test (or the Fisher exact test when appropriate). For continuous variables, we will use the independent sample *t* test (if the distribution is not normal, we will use the Mann-Whitney *U* test). Student’s *t* test will be used to compare means and odds ratios (ORs), and 95% confidence intervals (CIs) will be estimated as well. ORs will be used with the data reported from the knowledge questionnaire, to establish the association between receiving or not receiving the intervention and improving or not knowing. Spearman’s correlation will be used to identify the association for test and re-test reliability. Multivariable analyses will be performed to explain the association of multiple variables with the factors significantly related to the primary outcome (such as the job profile of the pharmacy staff, and others that will be considered as relevant variables). The McNemar tests will be used to analyze the difference in scores of the competency’s questionnaire of skills and attitudes and the scores of the knowledge questionnaire. All statistical tests will be computed using the Statistical Package for the Social Sciences (version 23; SPSS, Chicago, IL, USA) with significance defined as a *p* < 0.05.

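### The between-arm tests named are not adjusted for the baseline score or the stratifying zone, and knowledge is partly reduced to improved or not, so precision the trial has already collected is given up

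*Protocol article*

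**What the plan says.** All references are to the protocol article.

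- **Trial design:** "The geography zone (neighborhoods) will be randomized stratified".
- **Outcomes and Data collection:** staff competencies are measured in both arms at baseline and at 12 months, and "The same questionnaires will be used in T0 and T12 for the pharmacy staff and the patients or caregivers". The simulated-patient assessment is also made at both times.
- **Community pharmacy staff competencies:** knowledge is a 50-item test with each item right or wrong, and skills and attitudes are 100 items on a four-point scale. Both yield numeric totals.
- **Statistical methods:** continuous variables go to an independent-sample t test or Mann-Whitney test, and categorical variables to chi-square or Fisher. For knowledge, arm is related to a yes/no record of improvement: "ORs will be used with the data reported from the knowledge questionnaire, to establish the association between receiving or not receiving the intervention". McNemar tests are named for differences in the questionnaire scores. A multivariable analysis is planned to explain associations with factors found significantly related to the primary outcome. It gives job profile as the example and leaves room for other relevant variables.
- **Sample size:** a gain is assumed for the programme arm ("expected to improve the pharmacy staff competencies in the intervention group at least 30" per cent), with half that figure assumed for controls ("in the control group by 15% (less in improving or increasing competencies"). The result is that "it is necessary to include at least 121 drugstores or drugstores/pharmacies in each group".

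**The concern.** Two pieces of information that usually sharpen an arm comparison are in hand: each participant's score on the same instrument before the intervention, and the factor on which randomisation was stratified. No between-arm comparison named in Statistical methods is adjusted for either. The planned multivariable analysis does not fill the gap. Its purpose is explanatory, its factors are tied to observed significance, neither the T0 score nor zone is named, and no adjusted arm effect is promised. McNemar tests are paired comparisons of binary results and do not estimate a difference between arms.

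The odds ratio also turns a score change into improved or not, so a gain of one item and a gain of twenty may count the same, depending on a definition the section does not give.

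At stake is the width of the interval around the main result, and whether a chance difference between arms at T0 carries into it.

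**Working it through.** **1. Reproducing the planned sample size.** Inputs from Sample size: 30% and 15%, read here as proportions improving; "With a confidence level of 95% and a power of 80% and superiority design". Sidedness is not stated; two-sided 0.05 is used. With pooled variance under the null and a mean proportion of 0.225:

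n = [1.960 × √(2 × 0.225 × 0.775) + 0.842 × √(0.30 × 0.70 + 0.15 × 0.85)]² / 0.15² = (1.157 + 0.489)² / 0.0225 ≈ 120.5, so **121 per arm**.

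For losses ("To cover losses to follow-up, the sample was increased by 10" per cent): 121 / 0.90 = 134.4, so **135**. Both stated figures reproduce. A one-sided test would give 95 and a continuity correction 134, so the plan rests on a plain two-sided comparison of two proportions. At 121 per arm its power is 80.2%.

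**2. Gain from adjusting for the T0 score.** The protocol gives no T0-T12 correlation r, so 0.3, 0.5 and 0.7 are assumed, with equal variance σ² at both times. The variance per participant is:

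- T12 score only: σ²
- change score: 2(1 − r)σ²
- T12 adjusted for T0: (1 − r²)σ²

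The adjusted variance is therefore a fraction 1 − r² of the T12-only variance, and (1 + r)/2 of the change-score variance.

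| r | Left, v T12-only | Cut, v T12-only | Left, v change | Cut, v change |
|---|---|---|---|---|
| 0.3 | 0.91 | 9% | 0.65 | 35% |
| 0.5 | 0.75 | 25% | 0.75 | 25% |
| 0.7 | 0.51 | 49% | 0.85 | 15% |

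For scale, take the effect that gives a T12-only t test 80% power at 121 per arm: (1.960 + 0.842) × √(2/121) = 0.360 SD. This is a reference value chosen here, not a figure from the protocol.

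| r | T12-only power | Change-score power | Adjusted power | Adjusted n for 80% |
|---|---|---|---|---|
| 0.3 | 80% | 65.8% | 83.6% | 111 |
| 0.5 | 80% | 80.0% | 89.9% | 91 |
| 0.7 | 80% | 95.1% | 97.5% | 62 |

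The adjusted analysis is the most precise in every row. How far ahead it is depends on r and on which t test is meant.

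**3. Cost of improved or not.** Suppose 30% v 15% improved comes from a normal change score cut at one threshold. The shift between arms is z(0.85) − z(0.70) = 1.036 − 0.524 = 0.512 SD of change. Kept continuous:

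n = 2 × (1.960 + 0.842)² / 0.512² = 15.70 / 0.262 ≈ 59.9, so **60 per arm**, against 121 for the binary comparison. Power at 121 would be 97.8%.

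With T0 adjustment as well, n = 59.9 × (1 + r)/2, which is 39, 45 or 51 per arm at r = 0.3, 0.5 or 0.7.

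**4. Zone.** No between-zone variance is given, so this gain cannot be computed.

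**The case against.** The case on the other side is substantial in several respects.

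- **T0 is not unused.** Improved or not is defined against T0, and pre-post analyses are planned. A reader might infer that the baseline is ignored; the accurate statement is that no arm comparison is adjusted for it. This stands.
- **The tests are valid and the trial is not shown to be underpowered.** A reader might take the loss from dichotomising to mean that the planned odds ratio has poor power. On the protocol's own 30% v 15% it has about 80% at 121 per arm. This stands.
- **Knowledge is not only dichotomised.** The t or Mann-Whitney test would cover the 50-item total, and the section does not call the odds ratio the main estimate. This stands, though neither route is adjusted.
- **Intervals are not necessarily too wide.** Ignoring zone widens them only if zones differ in outcome. Drugstores may contribute more than one staff member, and ignoring that clustering acts in the other direction, so the net direction is unknown. This stands.
- **No ceiling effect is shown.** The documents give no T0 scores, so nothing supports a claim that staff near the maximum are penalised.
- **The multivariable wording leaves room for T0 and zone, and covariate lists are often left to an analysis plan.** This is true in part. But the section is not silent: it names the between-arm tests, and its only adjusted analysis ties its factors to significance. The point is about what is stated.

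**Conclusion.** The point holds as a matter of efficiency. The between-arm analyses named are valid for a randomised comparison, but they give up precision and leave chance T0 imbalance in the estimate. The documents do not support calling them biased, invalid or underpowered.

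The gain from T0 adjustment ranges from 9% to 49% of the variance if the t test is on T12 scores, and from 35% down to 15% if it is on change scores, over assumed correlations of 0.3 to 0.7. The direction does not depend on the correlation; the size does. The contrast of about 60 v 121 per arm rests on a normal change score and on reading 30% and 15% as proportions improving, a reading supported by the exact reproduction of 121. The benefit from zone is unquantified and depends on zones differing in outcome.

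This should be changed, but the trial's validity does not depend on it.

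**What to change.** In Statistical methods, make the main between-arm analysis a linear model of the T12 score on arm, T0 score and geographic zone. Report the adjusted mean difference with its 95% confidence interval, and apply the model to the knowledge, skills/attitudes and simulated-patient scores. Where zones are sparse, group them by a rule fixed before the analysis. Where a drugstore contributes several staff, add a drugstore random effect or use cluster-robust standard errors.

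Keep the odds ratio, with a fixed definition of improvement, as a supportive analysis that matches the sample-size assumption. State that the multivariable analysis of factors related to the outcome is exploratory.

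**Cost:** no new data, since all the variables are already collected or known from randomisation. The zone grouping has to be written down. The headline measure becomes a mean difference, no longer the proportion improved on which the sample size was based, and the text should say so. Trial status describes the study as still in intervention and follow-up, so the change can be dated and recorded before the analysis.

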#### Community pharmacy staff competencies (knowledge, skills, and attitudes)

For the measurement of knowledge, a self-applied questionnaire of 50 multiple-choice questions (4 possible answers) with only one answer was constructed, and it will be categorized as correct or incorrect. The questionnaire will have the following topics: (1) pharmaceutical terminology and basic pharmacology, (2) pharmaceutical legislation, (3) technical and administrative management of the pharmacy, (4) communication and health education from the pharmacy, (5) good practices of dispensing and proper use of medicines, (6) pharmacovigilance from the pharmacy, and (7) pharmaceutical intervention on some common diseases in pharmacy (depression, anxiety disorder, sleep disorders, and pain management).

For the measurement of skills and attitudes, a self-applied questionnaire of 100 questions or performance criteria was constructed, which will be evaluated according to the frequency in which it will perform. For this purpose, a Likert scale will be established with four possible options: never (1), sometimes (2), usually (3), or always (4) that evaluate the following competencies—(a) provision of patient care: initial contact with the patient, medical prescription, medication needs, medication reconciliation, medication supply, use of guidelines and protocols, drug specifications, drug interactions, information about medications and patient education, additional activities, identification of drug-related problems, patient care, and evaluation of results; (b) personal: personal organization, practical communication skills, teamwork, and professionalism; (c) problem-solving: access related to information, knowledge, information analysis, and monitoring the patient; and (d) management and organization: clinical management and pharmacological safety, service provision, acquisition, and satisfaction of the services offered.

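### Spearman's correlation is the only statistic named for test-retest reliability; it cannot show a systematic shift between sittings, so it could overstate how well repeat scores agree

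*Protocol article*

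**What the plan says.** In the protocol article, Statistical methods assigns one statistic to repeatability: Spearman's "correlation will be used to identify the association for test and re-test reliability". It does not say which instrument, sample or retest interval is meant, and it sets no value that counts as acceptable. No ICC, kappa, limits of agreement or standard error of measurement appears anywhere in the article.

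The section on staff competencies describes two new instruments. For knowledge, "a self-applied questionnaire of 50 multiple-choice questions (4 possible answers) with only one answer was constructed", each item scored correct or incorrect. For skills and attitudes, "a self-applied questionnaire of 100 questions or performance criteria was constructed", each rated from 1 to 4. Under Outcomes, these two questionnaires measure the primary outcome, with the simulated patient technique in addition.

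Under Data collection, "The same questionnaires will be used in T0 and T12 for the pharmacy staff and the patients or caregivers". The same section adds one further measurement, in the intervention group only, 12 months after follow-up ends. The only other check of the instruments described there is an expert review of content validity. Statistical methods plans both pre-post analyses and between-group comparisons for all outcomes.

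**The concern.** A rank correlation asks whether people keep their order from one sitting to the next. Test-retest reliability of a score used to measure change also asks whether the same person obtains about the same score when nothing real has changed. Any increasing transformation of the second score leaves Spearman's coefficient untouched, so a uniform practice gain is invisible to it.

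Practice gains are plausible here because the same multiple-choice test is given more than once. Such a gain would look like improvement in a pre-post comparison. A high Spearman coefficient might be offered as reassurance that the questionnaire is stable when it carries no information on that point.

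**Working it through.** **The plan's own figure.** The article gives no reliability coefficient or threshold to reproduce. Its one computable figure is the sample size. With 30% against 15%, two-sided alpha 0.05, power 80% and pooled variance under the null (mean proportion 0.225):

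n = [1.960 × √(2 × 0.225 × 0.775) + 0.842 × √(0.30 × 0.70 + 0.15 × 0.85)]² / 0.15² = 120.5, rounded up to 121 per group.

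Allowing for 10% loss, 121 / 0.9 = 134.4, rounded up to 135. Both match Sample size in the protocol article. No reliability term enters, so this point does not touch them.

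**Inputs for the comparison.** The 0 to 50 range of the knowledge score comes from the article. The rest is assumed, because the article gives no SD, error or practice effect: true between-person SD 6 items (variance 36), error SD 2 items (variance 4), and a constant shift of d items at the second sitting. Scores are treated as normal, with no ceiling.

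**Spearman.** The Pearson correlation between sittings is 36 / (36 + 4) = 0.90 for any d. Under normality, Spearman = (6/π) × arcsin(0.90/2) = 0.89, also for any d.

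**Absolute-agreement ICC.** For two sittings that differ by d, the between-sitting variance is d²/2, so ICC = 36 / (36 + 4 + d²/2).

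| Shift d (items) | Spearman | ICC |
|---|---|---|
| 0 | 0.89 | 36/40 = 0.90 |
| 3 | 0.89 | 36/44.5 = 0.81 |
| 5 | 0.89 | 36/52.5 = 0.69 |

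**Sensitivity to the assumptions.** Take true SD 5 and single-score reliability 0.90 instead (true variance 25, total variance 25/0.90 = 27.78). A simulation of 200,000 pairs gave Spearman of about 0.89 throughout, with ICC 0.90, 0.81, 0.62, 0.45 and 0.32 for shifts of 0, 2.5, 5, 7.5 and 10 items. The formula agrees: at d = 5, 25 / (27.78 + 12.5) = 0.62. The ICC at a given shift depends on the assumed SD; the direction does not.

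**Where a shift reaches the trial's results.** Suppose a practice gain of d is common to both arms. Each arm's pre-post change then contains the full d. In the difference between arms it cancels (d − d = 0), unless ceiling effects or different practice make it unequal.

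**The case against.** The strongest reply is that little depends on this coefficient. The plan attaches no threshold or decision to it. For comparing randomised arms, consistent ranking is a defensible property to check, a common shift largely cancels, and the control arm's own pre-post change would contain any practice gain. This stands, and it is why the point is minor. It does not make Spearman a measure of agreement, and the plan also announces pre-post analyses, where a shift does not cancel.

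It is also fair that the gap depends on assumption: with no shift, 0.89 and 0.90 tell the same story. The point therefore concerns what Spearman could hide, and does not show that it hides anything here.

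A reader might infer that baseline and 12-month scores will be correlated and presented as reliability. The article does not say so. It repeats the questionnaires at those times but does not name the retest data. The questionnaires went through separate development work, in which a short-interval retest is neither stated nor excluded, and a journal article may leave such detail to the full protocol. Nor are those two occasions the only ones, given the later intervention-group measurement. That measurement is meant to show whether effects last, so it would not make a clean retest either.

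**Conclusion.** The point holds in a limited form. The protocol names a rank correlation for test-retest reliability and nothing that measures agreement. If scores shift systematically on repeat, the coefficient could overstate the reliability of the questionnaires that carry the primary outcome. Under the assumed SDs of 6 and 2, the gap between Spearman and the ICC is about 0.08 at a 3-item shift and 0.20 at a 5-item shift, and practically nil with no shift. Those sizes rest on the assumed SDs and a constant shift without ceiling; the insensitivity of Spearman to such a shift does not.

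The documents do not support saying that reliability will be overstated, since that needs a shift nobody has yet shown. The consequence is confined to a supporting check on the instruments and to the reading of pre-post changes. The sample size is unaffected and the randomised comparison largely so.

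**What to change.** In Statistical methods, state that on whatever retest data exist, the total knowledge score and the total skills-and-attitudes score will each be summarised by a two-way, absolute-agreement, single-measurement ICC with 95% CI, together with the mean difference between sittings. Keep Spearman only as a supplement. Name the sample and interval of the retest data used.

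Add that measurements a year or more apart that span the intervention will not be presented as test-retest evidence, because real change and measurement error cannot be separated in them. If no suitable retest was done, report that reliability over repeat sittings was not assessed.

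The cost is a few lines of text and one short analysis. No new data collection is asked for; Trial status says that the trial is already in intervention and follow-up, so adding a retest now would not be a small change. The small downside is that the reported reliability may be lower than Spearman alone would show.

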### Recruitment

#### Drugstores or drugstores/pharmacies and pharmacy staff

We will invite the pharmacy staff of 700 drugstores and drugstores/pharmacies to participate in the study. The researchers will explain to the pharmacy staff the objectives and the study design in meetings where they will accept their participation. Besides, all drugstores and drugstores/pharmacies will be visited by a pharmacist (no researcher) to obtain their written consent, between December 2018 and January 2019. The drugstores and drugstores/pharmacies that do not attend the meetings will be called by phone by a researcher to invite them to the rehearsal, and then they will be visited. If neither pharmacy staff of drugstores and drugstores/pharmacies do not agree to participate in the trial, they will be replaced by another from the same geographic area. Pharmacy staff will not receive any economic compensation for participating in the study. The researchers will ensure that the data collected is anonymous and strictly confidential.

The inclusion and exclusion criteria of pharmacy staff that accept to participate in the study will be evaluated. Some of their demographic and academic characteristics will be recorded: age, sex, highest educational level, year of pharmacist title (if applicable), university or educational institution where degree was obtained (if applicable), function in the pharmacy (owner/worker), hours worked per week, continuing education in recent years, the intensity of continuing education, time of experience as a pharmacy staff, and if they currently live in the same neighborhood as the drugstores or drugstores/pharmacies where they are employed.

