### Outcomes

Pharmacy staff competencies (knowledge, skills, and attitudes) will be assessed using two self-applied questionnaires. The measurements will be performed at baseline (T0) before the intervention and 12 months (1 year) after completing the follow-up (T12). Additionally, the simulated patient technique will be used to evaluate the skills and attitudes of the pharmacy staff in the dispensation and the information supply for the correct use of drugs (T0 and T12).

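### The multivariable analysis, as most naturally read, picks staff factors by their significance with the primary outcome and tests them at p < 0.05 in the same data, so its claims about factors are not valid as confirmatory results

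*Protocol article*

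**What the plan says.** The Statistical methods section of the protocol article says that "Multivariable analyses will be performed to explain the association of multiple variables with the factors significantly related to the primary outcome". A parenthesis follows: "such as the job profile of the pharmacy staff, and others that will be considered as relevant variables". The section closes by setting one level for every test, "significance defined as a *p* < 0.05". It names no multiplicity adjustment and does not call the multivariable work exploratory.

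The pool from which factors could come is in the Recruitment section: "Some of their demographic and academic characteristics will be recorded: age, sex, highest educational level", followed by items that include "hours worked per week, continuing education in recent years, the intensity of continuing education, time of experience as a pharmacy staff". With year of title, institution, role as owner or worker, and whether the person lives in the neighbourhood, the list has 11 characteristics. Two of these (year of title and institution) are marked as applying only to some staff, which leaves 9 for everyone.

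The primary outcome is measured in more than one way. Under Outcomes, "Pharmacy staff competencies (knowledge, skills, and attitudes) will be assessed using two self-applied questionnaires", and a simulated patient assessment of skills and attitudes is added.

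**The concern.** A covariate list can properly be left to a statistical analysis plan. Here, though, the protocol supplies the criterion itself: a factor qualifies by being significant with the outcome, or by being thought relevant later. An analysis plan that followed this wording would keep the problem, and one that fixed the list in advance would have to replace the wording.

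When the same data choose a factor and then test it, the reported p-value takes no account of the choice. Only associations that happened to look large reach the model, so their estimates are biased away from zero and their intervals do not have 95% coverage. A chance association between, say, hours worked and the knowledge score could be presented as a finding about which staff have better competencies. The Discussion stresses that around 60% of staff in the earlier survey had no technical or professional title, so statements about staff profile are a likely product of this trial.

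**Working it through.** **1. The plan's own design figure.** The article gives no error rate for factor selection. Its one reproducible figure is the sample size, used here only to set N. For 30% against 15%, two-sided 5%, power 80%, pooled variance and no continuity correction:

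n = [1.960·√(2·0.225·0.775) + 0.842·√(0.30·0.70 + 0.15·0.85)]² / 0.15² = 120.5, so 121 per group. Allowing 10% loss: 121 / 0.90 = 134.4, so 135. Both agree with the article. The simulation uses N = 2 × 121 = 242, one staff member per drugstore.

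**2. Chance that a null factor passes the screen.** For k independent tests at 0.05 with no true association, the chance of at least one pass is 1 − 0.95^k:

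- k = 9 (characteristics that apply to everyone): 1 − 0.95^9 = 37%
- k = 11 (all recorded characteristics): 1 − 0.95^11 = 43%

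With 11 equally correlated factors the rate falls to about 38% at pairwise correlation 0.3 and about 30% at 0.5.

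**3. Chance that a null factor is still significant after refitting.** In the simulation, 11 null factors are each screened against the outcome at p < 0.05. Those that pass are entered in a linear model with arm and tested again at p < 0.05. The table gives the share of trials with at least one null factor still below 0.05.

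| Arm effect (assumed) | correlation 0 | 0.3 | 0.5 |
|---|---|---|---|
| none | 41% | 30% | 19% |
| 0.4 SD | 38% | 26% | 15% |
| 0.8 SD | 31% | 21% | 12–13% |

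Repeat runs differ by one or two percentage points; one independent run with an arm effect of 0.4 SD and uncorrelated factors gave 35–36%. The range is about 13% to 41%. The rate falls as the arm effect grows because the screen ignores arm and the refitted model does not. In that same run (0.4 SD, uncorrelated factors) about 78–80% of the factors selected by chance stayed significant, so refitting gives little protection there. It protects more when factors are correlated.

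**4. Effect on the arm comparison.** With no true arm effect, if either the unadjusted or the adjusted arm result could be quoted, the false-positive rate is 5.6–5.8%, close to the nominal 5%.

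**5. For comparison.** If all 11 characteristics were tested with a Bonferroni level of 0.05/11 = 0.0045, the chance of any false finding would be about 5%.

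**The case against.** The strongest reply is that the selection rule is inferred. Read literally, the sentence relates a set of variables to the significant factors; it does not say that the significant factors are admitted to a model. No univariable screen, entry threshold or model type is given. Job profile is named before any T12 data exist, and the remaining variables enter by judgement of relevance. On that reading all that is left is an unspecified covariate list, which is ordinary content for an analysis plan. The wording is indeed garbled, and job profile is less exposed than the rest. But selection by significance remains the most natural reading, and the judgement route is open-ended too, so it does not repair the rule.

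Four further objections stand and limit the point:

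- The 11 candidates come from a description of recruitment. The article never says that all of them will be screened.
- A reader might infer that findings on who responds to the programme are at risk. The article describes no interaction or subgroup analysis by staff profile, so this is not supported. It plans no adjusted arm analysis either, and none of its four objectives concerns staff predictors of competence.
- A reader might set the rates above against the article's 5% and call them a several-fold breach. The article's 5% is a per-test level, and it promises no family-wise level for factors.
- Screening 11 factors on three measures would give 1 − 0.95^33 = 82%, but only if all 33 tests were independent. The same staff supply every measure and several characteristics overlap, so this is an upper bound and not an expected rate.

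**Conclusion.** The point holds as a badly fixed rule with limited reach. On the most natural reading, factors are selected and tested in the same data at p < 0.05 without correction or an exploratory label, and their p-values and intervals are not valid. If the 11 recorded characteristics were screened on one outcome and none mattered, at least one would pass in about 30% to 43% of trials and at least one would survive refitting in about 13% to 41%. These figures rest on the assumed pool of 11, correlations from 0 to 0.5, an arm effect from 0 to 0.8 SD, and every factor being null. If some factors truly matter, as education or training may, not every reported association would be chance.

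It would go too far to infer that the trial's main result is compromised: the randomised comparison is barely affected. The change is worth making because it is cheap, not because a primary conclusion depends on it.

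**What to change.** In Statistical methods, replace selection by significance with a model fixed before T12 data are seen: arm, T0 score, geographic zone and job profile. T0 scores are already collected (Outcomes), zone is already the stratification factor (Trial design), and job profile is already named in the sentence at issue. Then state that associations of the other recorded staff characteristics with competencies are exploratory, and that all of them will be shown as estimates with 95% CIs whatever their p-value.

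This takes one or two sentences and no new data. The downside is that these associations can no longer be claimed as established.
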